# Adjunctive use of physostigmine salicylate (Anticholium®) in perioperative sepsis and septic shock: study protocol for a randomized, double-blind, placebo-controlled, monocentric trial (Anticholium® per Se)

**DOI:** 10.1186/s13063-017-2231-x

**Published:** 2017-11-10

**Keywords:** Physostigma venenosum, Antilirium, Cholinesterase inhibitor, Continuous administration, Eserine, Eseroline, Intra-abdominal infection, Critically ill, Cholinergic anti-inflammatory pathway, Sequential Organ Failure Assessment (SOFA) score

## Abstract

**Background:**

Severe sepsis and septic shock remain a major challenge, even in modern intensive care. In Germany, about 68,000 patients die annually because of septic diseases, characterized by a complex systemic inflammatory response. Causal treatment of the underlying infection is essential for successful management of sepsis, but the course can be positively influenced by supportive and adjuvant measures. The cholinergic anti-inflammatory pathway (CAP) represents a new approach to adjunctive therapy of septic diseases and can be pharmacologically activated by the acetylcholinesterase inhibitor physostigmine (Anticholium®). Promising effects can be found in several in vitro and in vivo models of sepsis, such as a reduction in pro-inflammatory cytokines and improved survival.

**Methods:**

Anticholium® per Se is a randomized, double-blind, placebo-controlled, monocentric trial to assess whether the CAP can be transferred from bench to bedside. In this pilot study, 20 patients with perioperative sepsis and septic shock as a result of intra-abdominal infection are enrolled. According to randomization, participants are treated with physostigmine salicylate (verum group) or 0.9% sodium chloride (placebo group) for up to 5 days. The mean Sequential Organ Failure Assessment (SOFA) score during treatment and subsequent intensive care of up to 14 days is used as surrogate outcome (primary endpoint). Secondary outcome measures include 30- and 90-day mortality. An embedded pharmacokinetics and pharmacodynamics study investigates plasma concentrations of physostigmine and its metabolite eseroline. Further analyses will contribute to our understanding of the role of various cytokines in the pathophysiology of human sepsis. A computer-generated list is used for block randomization.

**Discussion:**

This randomized, controlled, monocentric trial investigates for the first time the adjunctive use of physostigmine (Anticholium®) in patients with perioperative sepsis and septic shock and may be a pivotal step toward the clinical use in this indication.

**Trial registration:**

EudraCT Number: 2012-001650-26 (entered 14 August 2012), ClinicalTrials.gov identifier: NCT03013322 (registered on 1 Jan 2017).

**Electronic supplementary material:**

The online version of this article (doi:10.1186/s13063-017-2231-x) contains supplementary material, which is available to authorized users.

## Background

### Background and rationale

In Germany, septic diseases kill approximately 68,000 patients each year [1]. About 280,000 (335 of 100,000) contract sepsis, approximately 115,000 of whom (138 of 100,000) experience severe sepsis or septic shock [1]. For those with severe sepsis, the probability of dying in hospital is about 44%, and increases to 59% for septic shock [1].

In view of these alarming figures, new approaches in treatment are required. One new treatment concept is based on the results of the group of Tracey [2].

In an in vitro test series with lipopolysaccharide (LPS)-treated human macrophage cultures, acetylcholine, the neurotransmitter of the parasympathetic nervous system, significantly inhibited the release of various pro-inflammatory cytokines, such as tumor necrosis factor (TNF)-α, interleukin (IL)-1β, IL-6, and IL-18, but not the anti-inflammatory cytokine IL-10 [2]. Suppression of TNF-α was reversed with α-bungarotoxin, but not with atropine, a specific muscarinic inhibitor [2]. Additionally, the peripheral vagus nerve was stimulated electrically, i.e., directly, in rats that had received the endotoxin intravenously. Stimulation of the parasympathetic nerve inhibited TNF-α synthesis in the liver and decreased peak serum TNF-α [2]. The decrease in blood pressure following endotoxemia was reduced significantly, and consequently, the progression from sepsis to severe sepsis and septic shock [2]. Thus, the inflammatory response can be influenced via α-bungarotoxin-sensitive nicotinic acetylcholine receptors.

These results have been confirmed by other groups in various sepsis models and have deepened our understanding of the cholinergic anti-inflammatory pathway (CAP) [3].

Taking into account the toxicity of the substances, concentrations used in test series, and ethical reservations about the direct electrical stimulation of the vagus nerve, the CAP must be accessible for patients in a different way.

Physostigmine salicylate is a peripherally and centrally acting inhibitor of acetylcholinesterase, and has been licensed and in clinical use for many years [4]. Acetylcholinesterase catalyzes the cleavage of acetylcholine to acetate and choline. Via decreased cleavage of the endogenous neurotransmitter, it thus alters acetylcholine levels. In an in vivo test series with mice that had undergone cecal ligation and puncture (a recognized sepsis model), we showed that physostigmine salicylate significantly inhibited the release of various cytokines (TNF-α, IL-1β, and IL-6); similar to the results of the group headed by Tracey [3]. Binding activity of nuclear factor (NF)-κB, a specific transcription factor, and activity of myeloperoxidase, a measure of pulmonary neutrophil invasion, was also attenuated [3]. The treatment diminished the decrease in blood pressure following infection, and lethality was reduced to the same extent as with nicotine [3]. Thus, the inflammatory response can be influenced by the use of physostigmine salicylate and this well-tolerated drug reduces the mortality in what is sometimes called the standard model for polymicrobial sepsis [5].

Pharmacological properties of physostigmine have been studied in animals including guinea pigs and of course rats, and humans [6]. The pyrroloindole alkaloid is predominantly metabolized in the liver and for a lesser part hydrolyzed by plasma esterases, with a respective half-life of 18–30 min. Metabolites are excreted with urine and feces [7].

Usually, physostigmine is administered by intravenous injection or short infusion. A few studies describe continuous infusion [4, 8, 9]. However, reliable pharmacokinetics and pharmacodynamics (PK/PD) data are still sparse, especially for patients with sepsis and septic shock. Note that the human subjects mentioned earlier were healthy volunteers [9] and some patients with Alzheimer’s disease [8]. In patients with sepsis and septic shock, however, the distribution, metabolism, and excretion of drugs are altered by complex and sometimes opposing changes and mechanisms including fluid extravasation, hemodynamic instability, and organ failure [10], possibly influencing pharmacodynamic effects [11].

This randomized, double-blind, placebo-controlled, monocentric pilot study on the use of physostigmine salicylate (Anticholium®) as an adjunctive measure in perioperative sepsis and septic shock is conducted to provide evidence of the effectiveness of physostigmine in humans - a clinical trial on an approved drug in a new indication.

Plasma concentrations of physostigmine and its metabolite eseroline are determined and a population pharmacokinetic model will be developed. Furthermore, cholinesterase activity is studied as a direct pharmacodynamic effect of physostigmine.

Further analyses will illuminate the role of various cytokines in the pathophysiology of human sepsis.

### Objectives

Anticholium® per Se evaluates the effect of treatment with physostigmine salicylate or drug-free placebo on the mean Sequential Organ Failure Assessment (SOFA) score (at least two individual values) during treatment and subsequent intensive care of up to 14 days in critically ill patients with perioperative sepsis and septic shock due to intra-abdominal infection, to assess whether the CAP can be transferred from bench to bedside.

## Methods: participants, interventions, and outcomes

### Trial design

Anticholium® per Se is a prospective, randomized (1:1), double-blind, placebo-controlled, monocentric pilot study. Only patients with perioperative sepsis and septic shock as a result of intra-abdominal infection are eligible. Participants are randomly assigned to one group that receives physostigmine salicylate (verum group), or to the other group that receives 0.9% sodium chloride (placebo group). The treatment period is at most 5 days, and follow-up is limited to 90 days. The mean SOFA score (at least two individual values) during treatment and subsequent intensive care of up to 14 days is used as surrogate outcome (primary endpoint). Secondary outcome measures include 30- and 90-day mortality. An embedded PK/PD study investigates plasma concentrations of physostigmine and its metabolite eseroline.

### Study setting

Anticholium® per Se is conducted in the Department of Anesthesiology, Heidelberg University Hospital. The Interdisciplinary Operative Intensive Care Unit (IOPIS) is a 16-bed ICU that admits a wide variety of surgical patients. This ICU handled 1556 admissions in the past 2 years, with an artificial ventilation ratio of approximately 60%. The executing clinic is monitored by the local Coordination Centre for Clinical Trials (KKS), which is responsible for study management and medical device safety. Data management and statistical analysis are provided by the Institute for Medical Biometry and Informatics (IMBI), Heidelberg.

### Eligibility criteria

Inclusion and exclusion criteria for participants are provided in Table 1.

**Table 1 Tab1:** Eligibility criteria for participants

Inclusion criteria	Exclusion criteria
• Age 18–85 years • APACHE II score < 34 • Intra-abdominal infection ◦ findings of diffuse peritonitis or ◦ a circumscribed abscess • Perioperative sepsis and ◦ secure evidence of infection, ◦ clinically backed up or ◦ secured microbiologically ◦ ≥ 2 of the following four criteria: ▪ fever ≥ 38.0 °C or ▪ hypothermia ≤ 36.0 °C secured by rectal intravesical or intravascular measurement ▪ tachycardia ≥ 90/min ▪ tachypnea ≥ 20/min or ▪ hyperventilation secured by arterial blood gas analysis with PaCO_2_ ≤ 4.3 kPa or 33 mmHg or ▪ mechanical artificial respiration ▪ leukocytosis ≥ 12,000/mm^3^ or ▪ leukopenia ≤ 4000/mm^3^ or ▪ ≥ 10% immature neutrophils in the differential count • Shock (<24 h duration): necessary use of vasopressors despite adequate fluid resuscitation to keep systolic blood pressure ≥ 90 mmHg or mean blood pressure ≥ 70 mmHg • No more than one planned and/or one emergency procedure performed since admission (no repeated revisions) • No infaust prognosis of a primary or concomitant illness, expecting the death within the follow-up phase • No do-not-resuscitate order • Written informed consent of full-age patients/their legal guardian to participate (written consent, according to AMG)	• Known hypersensitivity to physostigmine salicylate, sodium metabisulfite, sodium EDTA, or any of the other ingredients of Anticholium® • Known contraindications [7] against Anticholium®: gangrene, coronary artery disease • Known absolute contraindications [7] against Anticholium®: myotonic dystrophy; depolarization block by depolarizing muscle relaxants; intoxication by “irreversibly acting” cholinesterase inhibitors; closed craniocerebral trauma; obstruction in the gastrointestinal tract (mechanical constipation); obstruction in the urinary tract (mechanical urinary retention) • Known relative contraindications [7] against Anticholium®: bronchial asthma; bradycardia; AV-conduction disturbances • Having undergone splenectomy • Having undergone solid organ transplantation • Positive pregnancy test, pregnancy, and lactation • Participation in another clinical trial, according to AMG or the follow-up phase of another study, according to AMG

*AMG* Medicinal Products Act, *APACHE* Acute Physiology And Chronic Health Evaluation, *AV* atrioventricular, *PaCO*
_*2*_ partial pressure of carbon dioxide

### Interventions

Participants are enrolled within 24 h of onset of shock as defined in Table 1. Study medication is commenced within the following 2 h. The treatment group receives an infusion of 0.04 mg/kg physostigmine salicylate with a maximum dose of 4 mg. The infusion is administered at 0.4 mg/min (=1 mL/min = 60 mL/h). The initial dose is followed by a continuous infusion of 0.017 mg/min, i.e., 1 mg/h (=0.042 mL/min = 2.5 mL/h) for 2–5 days, i.e., 48–120 hours (treatment phase). The placebo group is treated with 0.9% sodium chloride.

The continuous infusion should not be interrupted; not even for surgery. If it is, the interruption is recorded in the case report form (CRF). Any interruption for > 90 min (five elimination half-lives > 18 min in humans) is considered a protocol violation, and the protocol violation is recorded in the CRF. Any interruption for > 180 min (ten elimination half-lives > 18 min in humans) is considered a discontinuation of trial medication. If the continuous infusion is interrupted for > 90 but < 180 min, the initial dose is repeated before the continuous infusion is resumed for the remaining time.

Criteria for discontinuing trial medication for an individual participant on the part of the investigator include occurrence of adverse events or delayed observation of violation of eligibility criteria that let it appear medically advisable.

The protocol does not make any provisions regarding interventions that are permitted or prohibited during the trial.

### Outcomes

The mean SOFA score (at least two individual values) during treatment and subsequent intensive care of up to 14 days is used as surrogate outcome in critically ill patients with perioperative sepsis and septic shock due to intra-abdominal infection.

Secondary measures include duration of artificial ventilation and intensive care, length of stay, 30- and 90-day mortality, arterial and central venous blood gas analyses, partial pressure of arterial oxygen/fraction of inspired oxygen (PaO_2_/FiO_2_), platelet count, leukocyte count, creatinine, urea, total bilirubin, C-reactive protein, prothrombin time, D-dimer, procalcitonin, IL-6, thrombin-antithrombin complex, mean blood pressure and use of vasopressors (frequency and duration), renal replacement therapy (frequency and duration), Glasgow Coma Scale (GCS) score, Acute Physiology And Chronic Health Evaluation (APACHE) II score, Simplified Acute Physiology Score (SAPS) II score, and the occurrence of side effects such as nausea or vomiting, clinically relevant changes in heart rate or blood pressure (mainly hypotension), and clinically relevant changes in airway resistance (mainly bronchiospasms as a result of hypersensitivity reactions to the sodium metabisulfite contained in the investigational medicinal product - spontaneous breathing: acute dyspnea or artificial ventilation: clinically relevant decline in respiratory volume at constant pressure settings, or clinically relevant incline in peak or inspiratory pressures at constant respiratory volumes).

Laboratory values, except IL-6 and thrombin-antithrombin complex, are determined during routine clinical examination in the inter-laboratory proficiency tested Central Laboratory (CL), or with a respective point-of-care device provided by the CL (for blood gas analyses). IL-6 and thrombin-antithrombin complex (from citrated plasma) are determined in the investigator’s laboratory using commercially available enzyme-linked immunosorbent assay (ELISA) kits. Moreover, additional serum samples are retained for further analyses at a later date.

Microbiological analyses of potential pathogens including susceptibility tests are performed at Heidelberg University Hospital, Department of Medical Microbiology.

For the PK/PD study, heparinized plasma samples are collected during treatment phase and on the following day (visits 1–8, see Table 2). Plasma concentrations of physostigmine and its metabolite eseroline are determined with a validated high-performance liquid chromatography (HPLC) method [12]. Cholinesterase activity is determined with ChE check mobile (Securetec, Neubiberg, Germany) [13] from remaining material drawn for routine blood gas analyses (arterial samples). The point-of-care device is dedicated to photometric measurement of acetyl- and butyrylcholinesterase activity in whole blood.

**Table 2 Tab2:**
[figure not shown]
Flow chart of visits, interventions, and data collected for the outcomes

*AE* adverse events, *PD* pharmacodynamics, *PK* pharmacokinetics, *SAE* serious adverse events

^a^During administration of trial medication (initial dose), patients are continuously monitored by a physician attentive to the occurrence of side effects, AEs, and SAEs

^b^Marked visits do not include any additional collection of blood (no second tube for IL-6 and thrombin-antithrombin complex)

^c^Visit 1 including visit 1.1 with two blood samples [3 min after the start of the initial dose and at the end of the initial dose (±2 min)], visit 1.2 with three blood samples [10, 20, and 30 min after the start of continuous infusion (±2 min)], visit 1.3 with one blood sample [after 1 h (±10 min)]

^d^Visit 7 including visit 7.1 with one blood sample [at the end of the infusion period (±2 min)], visit 7.2 with three blood samples [10, 20, and 30 min after the end of the infusion period (±2 min)], visit 7.3 with two blood samples [after 1 and 2 h (±10 min)]

### Participant timeline

A flow chart of trial-specific procedures, assessments, and visits for participants is provided in Table 2.

The final visit is made on the day of discharge from ICU. In case of death, date of death is regarded as day of discharge from ICU and documented in the CRF accordingly. The final physical examination is omitted on the date of death. In all other cases, it is attempted to assess 30- and 90-day mortality, either from patient file or by telephone.

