### Statistical methods

The primary endpoint is the mean SOFA score during treatment and subsequent intensive care of up to 14 days in the intention-to-treat (ITT) population. Anticholium® per Se being a pilot study missing values will not be imputed. The ITT population will include all randomized participants (full analysis population) from whom the primary outcome measure was obtained. The two-sided analysis of covariance (ANCOVA) model will include age as continuous covariate.

The per protocol population will consist of all participants from the ITT population without serious protocol violation. These include violations against eligibility criteria or departures from the treatment scheme, especially falling short of the minimum duration of administration. Exceeding the maximum duration of administration is not considered a serious protocol violation. Any interruption for > 90 min but ≤ 180 min and interruptions for source control of infection are not considered serious protocol violations, unless the continuous infusion is paused earlier than 90 min before the beginning or continued later than 90 min after the end of the intervention.

The χ2 test (categorical data) and further ANCOVA (continuous data) will be used for further descriptive analysis and secondary outcome measures, which will also be tabulated (measures of location and dispersion as appropriate for underlying empirical distribution). The Kaplan-Meier method and log-rank test will be used for survival analysis. Estimates of effect and 95% confidence intervals will be reported where possible and descriptive *P* values given. In addition, graphs are presented where possible.

Secondary analyses will include all participants from whom the primary outcome measure was obtained.

In the PK/PD study, plasma concentrations of physostigmine and eseroline are used to develop a population pharmacokinetic model for continuous intravenous administration. Possible structural models are examined and the impact of potential covariates (e.g., body weight, height, and gender) is investigated. Furthermore, PK/PD correlation of physostigmine concentrations and plasma cholinesterase activity is investigated.

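### Durations cut short by death go into the same ANCOVA as durations ended by recovery, so an arm with more early deaths tends to show shorter, apparently better stays

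*Protocol article*

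**What the plan says.** The Outcomes section of the protocol article states: "Secondary measures include duration of artificial ventilation and intensive care, length of stay, 30- and 90-day mortality". Further down the same list come "use of vasopressors (frequency and duration), renal replacement therapy (frequency and duration").

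Statistical methods assigns the analysis by data type: "further ANCOVA (continuous data) will be used for further descriptive analysis and secondary outcome measures". Time-to-event methods are named for one purpose only: "The Kaplan-Meier method and log-rank test will be used for survival analysis". Secondary analyses take in everyone who has the primary measure. Since that measure needs only two SOFA values, a patient who dies early but after two scores is included.

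On death, Participant timeline says: "In case of death, date of death is regarded as day of discharge from ICU and documented in the CRF accordingly". This sentence concerns the ICU discharge date. It does not mention ventilation, vasopressors, renal replacement or hospital stay.

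The results are meant as description: "Estimates of effect and 95% confidence intervals will be reported where possible and descriptive" P values. Mortality at 30 and 90 days is reported in its own right.

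**The concern.** A short ICU stay or a short time on a ventilator is read as a good result. A patient who dies early also has a short stay and a short time on support. With the death date as the end of the ICU stay, and ANCOVA applied to the durations as recorded, the two kinds of short value count the same in a comparison of means. The no-imputation rule, "Anticholium® per Se being a pilot study missing values will not be imputed", does not remove these values, because a duration ended by death is observed and not missing.

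The population is one in which this can matter. Every participant must be in shock, and the article says that in severe sepsis "the probability of dying in hospital is about 44%, and increases to 59% for septic shock". If the arms differ in mortality, the estimated effects on ICU stay and organ support could favour the arm in which more patients died. The trial is meant to generate hypotheses for later work, so the direction of these estimates is what a reader will take from them.

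**Working it through.** The plan gives no figure for these outcomes. Its one sample-size figure, a detectable d of 1.32 with 10 per group, reproduces (two-sided t test with 18 df: power 79.7%; d for 80% power 1.325), but the point does not depend on it.

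**Inputs from the article**
- 10 patients per arm; ANCOVA with age as covariate is the model named for the primary endpoint.
- Hospital mortality of 44% and 59%, used here as the two arms purely for illustration.

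**Assumptions, not in the article**
- Mean ICU stay of survivors, L, is equal in both arms: 10 to 20 days.
- Mean time to death, t: 3 to 7 days.

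**Expected mean stay**

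With a proportion p dying, the mean recorded stay is (1 − p)L + pt. The difference between an arm with mortality p1 and one with p0 is −(p1 − p0)(L − t). At 44% v 59% this is −0.15 × (L − t).

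- L = 14, t = 5: 0.56 × 14 + 0.44 × 5 = 10.04 days against 0.41 × 14 + 0.59 × 5 = 8.69 days; difference −1.35 days.
- Smallest in the range, L = 10, t = 7: −0.15 × 3 = −0.45 days.
- Largest in the range, L = 20, t = 3: −0.15 × 17 = −2.55 days.
- Equal mortality: 0. If deaths come later than survivors' discharge (t > L), the sign reverses.

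**Behaviour in a trial of this size**

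Simulated ANCOVA with age as covariate, 10 per arm, 4000 runs, survivors' stay lognormal with mean 14 days, time to death exponential with mean 4 days:

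| Mortality | Mean difference in stay | Runs with shorter stay in the arm with more deaths | Runs significantly shorter | Difference in ICU-free days to day 30 (death = 0) |
|---|---|---|---|---|
| 44% v 59% | −1.4 d | 64% | 5% | −2.4 |
| 30% v 60% | −2.9 d | 78% | 12% | −4.9 |
| 20% v 70% | −5.0 d | 92% | 26% | −8.3 |

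At 44% in both arms, the mean difference was close to 0 and either arm was about equally likely to look shorter.

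**Chance imbalance**

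With equal true mortality of 44%, the standard deviation of the between-arm difference in deaths is √(2 × 10 × 0.44 × 0.56) = 2.2 patients. The 15-point gap used above is 0.15 × 10 = 1.5 patients. A gap of that order can therefore arise in a single trial with no drug effect on survival.

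**The case against.** The strongest reply is that Statistical methods assigns ANCOVA to continuous data in general and names no duration. How a secondary duration is derived when the patient dies is often settled in an analysis plan, which is not shown here. That stands as a caution: such a plan may already hold a rule. But the article does fix the method, the included patients and the ICU end date. Followed as written, these give the distorted comparison.

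The stakes are limited. These are secondary outcomes with descriptive P values in a pilot of 20, and mortality and survival curves stand beside them, so a careful reader could see an imbalance in deaths. This stands, and it is why the point concerns interpretation and not the trial's main test.

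The size rests on assumed stays and death times. At 44% v 59%, only 64% of simulated trials went the wrong way. The free-day column is also partly true by construction: with equal survivor stays it restates mortality. Both remarks are correct. The calculation shows a direction and a plausible range, not a forecast.

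A reader might infer three stronger things that the documents do not support:
- **That death and live discharge are merged in the CRF.** The same section omits the final examination on the date of death and seeks later mortality in all other cases. Deaths are also reported as serious adverse events and as mortality outcomes.
- **That the death-date sentence governs all durations.** It covers the ICU date only. The others are shortened because support stops at death.
- **That about half of all values are set by death.** The 44% and 59% are hospital mortality, and a death on the ward after ICU discharge does not shorten ICU stay. The eligibility criteria also exclude high APACHE II scores, hopeless prognosis and do-not-resuscitate orders.

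**Conclusion.** The point holds in limited form. ICU stay explicitly, and the other durations by implication, are shortened by death and then compared as if they had ended in recovery. The arm with more deaths will tend to show shorter durations on two conditions: mortality differs between the arms, and deaths come earlier than survivors' end of support. At 44% v 59% mortality the shift in mean ICU stay is −0.45 to −2.55 days over the assumed ranges. It is nil on average with equal mortality and could reverse if deaths are late. It should be corrected because the stated method can give estimates in the wrong direction. It does not touch the primary analysis.

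**What to change.** For these secondary outcomes, length of stay included, replace ANCOVA on raw durations by one of two analyses, fixed before unblinding:

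1. Days alive and free of ventilation, vasopressors, renal replacement, ICU or hospital to day 30, scored 0 for any patient who dies by day 30, compared by a rank-based method with an interval estimate (for example a Wilcoxon test with a Hodges–Lehmann interval).
2. Cumulative incidence of live discharge, or of live end of support, with death as a competing event.

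Two conventions need stating: how support after ICU discharge is counted, since the final visit falls on that day, and what is done when vital status at day 30 is unknown. Raw durations should still be reported, as description, separately for survivors and non-survivors.

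The cost is analysis wording and the derivation of a few variables from dates that the trial should already hold. No CRF change, visit or treatment change is needed. There are two downsides. A free-day score mixes mortality with duration, so both parts should be tabulated next to it. A simple rank test also gives up any covariate adjustment that the ANCOVA would have made.

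### Untraced vital status and the two-SOFA-value requirement can each bias 30- and 90-day mortality, and the net direction is undetermined

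*Protocol article*

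**What the plan says.** Mortality at 30 and 90 days is a secondary outcome (Trial design; Outcomes). The protocol article gives two routes for learning vital status, both under Participant timeline. For deaths in the ICU: "In case of death, date of death is regarded as day of discharge from ICU and documented in the CRF accordingly". For everyone else: "In all other cases, it is attempted to assess 30- and 90-day mortality, either from patient file or by telephone".

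The Statistical methods section then contributes four statements:

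- On missing data: "Anticholium® per Se being a pilot study missing values will not be imputed". This stands in the paragraph on the primary endpoint. No other rule is given for mortality.
- On tests: "The χ2 test (categorical data) and further ANCOVA (continuous data) will be used for further descriptive analysis and secondary outcome measures".
- On survival: "The Kaplan-Meier method and log-rank test will be used for survival analysis".
- On the analysis set: "Secondary analyses will include all participants from whom the primary outcome measure was obtained".

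The last statement takes its force from the definition of the primary outcome under Outcomes: "The mean SOFA score (at least two individual values) during treatment and subsequent intensive care of up to 14 days". A patient with fewer than two SOFA values has no primary outcome.

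**The concern.** Whether a patient's status is known depends partly on the outcome itself. Someone who dies in the ICU has a recorded date of death. Someone who leaves the ICU alive has a known status at day 30 or 90 only if the file or a telephone call supplies it. A χ² table without imputation cannot hold a patient whose status is unknown, so the loss falls only on patients who left the ICU alive.

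The restriction to patients with a primary outcome works at the other end. A patient who dies before a second SOFA value is excluded from the mortality comparison although the death is known.

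Mortality is the secondary outcome that the abstract and the Trial design section single out, and Sample size values the results for generating hypotheses. With 10 patients per arm, a shift of one or two patients is large compared with anything the rates could show.

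**Working it through.** **Inputs from the protocol article.** 10 patients per arm (Sample size); the ascertainment, testing and analysis-set rules set out above; hospital mortality of about 44% in severe sepsis and 59% in septic shock (Background).

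**Inputs assumed, because the article gives none.** The number of deaths per arm, the share of ICU survivors not traced, mortality after leaving the ICU, and the number of deaths before a second SOFA value.

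**The plan's own figure.** No figure is stated for mortality or for loss to follow-up. The only design calculation is a detectable d of 1.32 with 10 per group. A two-sided two-sample t-test with 18 degrees of freedom gives 79.7% power at that effect, so it reproduces. It has no bearing on this point.

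**Step 1: direction of the error from untraced patients.** Let f be the share dying in the ICU, q the later mortality in traced ICU survivors, m the share of ICU survivors untraced, and u the mortality among the untraced.

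- True mortality = f + (1−f)[(1−m)q + m·u]
- Complete-case mortality C = [f + (1−f)(1−m)q] / [1 − (1−f)m]
- Subtracting: C − true = (1−f)m × (C − u)

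The sign therefore depends only on whether u lies below or above C.

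Example with f = 0.44, q = 0.10, m = 0.20:

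- C = (0.44 + 0.56×0.80×0.10) / (1 − 0.56×0.20) = 0.4848/0.888 = 54.6%
- If u = q = 0.10, true mortality = 0.44 + 0.56×0.10 = 49.6%, so C is 5.0 points too high.
- If u = 1, true mortality = 0.4848 + 0.112 = 59.7% (0.5968), so C is 5.1 points too low.

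Over f from 0.30 to 0.59, q from 0.10 to 0.20 and m from 0.10 to 0.30:

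- With u = q, C is too high by 1.8 to 8.0 points.
- With every untraced patient dead, C is too low by 1.3 to 11.7 points.
- The sign changes where u equals C, which runs from 39% to 74% across these scenarios.

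**Step 2: whole patients, one arm of 10 with 5 deaths (true mortality 50%).**

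| What is lost | Proportion analysed |
|---|---|
| 1 untraced patient, alive | 5/9 = 55.6% |
| 2 untraced patients, alive | 5/8 = 62.5% |
| 1 untraced patient, in fact dead | 4/9 = 44.4% |
| 1 early death without a second SOFA value | 4/9 = 44.4% |
| 2 such early deaths | 3/8 = 37.5% |
| 1 early death and 1 untraced patient, alive | 4/8 = 50.0% |

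The last row shows that the two exclusions can cancel exactly.

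**Step 3: effect on the comparison between arms.**

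- Deaths in 6/10 and 4/10, one untraced living patient in each arm: the difference moves from 20.0 points to 6/9 − 4/9 = 22.2 points.
- Deaths in 5/10 and 3/10, 20% of survivors untraced in each arm, no later deaths: 5/9 = 55.6% and 3/8.6 = 34.9%. The risk difference moves from 20.0 to 20.7 points and the risk ratio from 0.60 to 0.63. The odds ratio stays at 0.43.
- Deaths in 5/10 in both arms, two living patients untraced in one arm only: 5/8 − 5/10 = a false difference of 12.5 points.

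Under equal proportional loss the comparison hardly moves. Unequal loss can create a difference where none exists.

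**The case against.** A reader might infer that the plan overstates mortality and so understates the benefit of a treatment that works. The documents do not support that. It would require every ICU death to stay in the table, whereas the analysis-set rule can remove early ones. It would also require untraced patients to be mostly alive, whereas a patient who cannot be reached by telephone may have died. Nor does shrinkage of the effect follow: in Step 3 the risk ratio moves slightly towards 1, while the risk difference widens slightly.

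Several other objections carry weight:

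- No sentence says that mortality in particular is compared by χ² on complete cases. The test sentence is generic, and the sentence on imputation stands in the primary-endpoint paragraph. Joining them is a reasonable reading, since the reason given (a pilot study) applies to the whole trial, but it is not an explicit rule.
- Kaplan-Meier and log-rank are already planned and can use an untraced patient up to the last contact. A reader might suspect censoring at ICU discharge, with the patient then given the hazard of those still in intensive care. The article states no such censoring rule, and the risk set would also hold traced patients already discharged. What remains is that censoring at last contact may be informative.
- The article is condensed, and tracing procedures are commonly left to the full protocol. A lack of detail on tracing is therefore not held against it here.
- Mortality is a secondary outcome with descriptive P values in a 20-patient feasibility pilot.

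These points limit the weight and remove any claim about direction. They do not touch what the text does state: ascertainment that depends on outcome, and an analysis set that can drop known deaths.

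**Conclusion.** The concern holds as a risk of bias of undetermined direction. Losing untraced patients raises the mortality proportion if they die less often than the complete-case rate, and lowers it otherwise. Requiring a primary outcome can remove known early deaths, which lowers it. In an arm of 10, one or two such patients shift the proportion by roughly 5 to 13 points (50% to between 37.5% and 62.5% in Step 2).

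This rests on three assumptions: that the no-imputation and χ² statements apply to mortality, that some patients go untraced, and that some die before a second SOFA value. The article gives no rate for the last two. The distortion of the comparison between arms is small if loss is proportionally equal and can be material if it is not. The primary endpoint is unaffected. For a secondary, descriptive outcome the point is moderate, and worth correcting because the correction is nearly free.

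**What to change.** In Statistical methods, state for 30- and 90-day mortality that:

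1. the analysis includes all dosed patients, whether or not two SOFA values exist (under Implementation, infusion of the initial dose is what makes a patient randomized);
2. the estimates at days 30 and 90 come from the Kaplan-Meier method already planned, with untraced patients censored at the last date known alive;
3. the number with unknown status is reported per arm and time point, with bounds that take all unknown as alive and all as dead. For an arm of 10 with 5 known deaths and 2 unknown, these are 5/10 = 50% and 7/10 = 70%;
4. a complete-case χ² test is not used as the mortality comparison. It can stay for the other categorical outcomes.

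The cost is a few lines of text, slightly more analysis and wider stated uncertainty. No additional data collection is needed. The bounds also cover the possibility that censoring at last contact is informative, which Kaplan-Meier alone does not resolve.
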